## **5. TREATMENT OF SUBJECTS**

This interventional study will involve an experimental device, experimental app and algorithms, and the collection of blood and/or mucus for testing with approved laboratory tests.

### **5.1 Investigational product/treatment**

Subjects will be randomly assigned to one of two sequences in which they will receive the experimental and control condition in random order. In the control condition, only data of the Daily Symptom Diary will be included in the feedback to the patient about their potential infection status; and in the experimental condition, both data of the Daily Symptom Diary and the Ava bracelet will be included in the feedback to the patient about their potential infection status. Subjects will be instructed to log symptom data in the Ava COVID-RED app (Daily Symptom Dairy) every day and wear their Ava bracelet throughout the study nightly while they sleep. Upon waking, they will synchronise the Ava bracelet to the corresponding Ava COVID-RED app on their smartphone. Subjects will receive real-time feedback in-app about their symptoms and in line with current Dutch national testing standards they should seek testing for SARS CoV2. Subjects will be blinded, which means that they will not know if the real time feedback about their potential infections status will come solely from the Daily Symptom Diary, or if this feedback is based on data from both the Daily Symptom Diary and the Ava bracelet.

### **5.2 Use of co-intervention (if applicable)**

Not applicable.

### **5.3 Escape medication (if applicable)**

Not applicable.

## 6. INVESTIGATIONAL PRODUCT

### 6.1 Name and description of investigational product(s)

Ava COVID-RED is an investigational product developed specifically for the COVID-RED clinical trial. The device uses machine learning and wearable sensor technology to help users monitor their general health and well-being. In particular, its algorithms are fine-tuned to detect changes in physiological and/or self-reported symptoms that could indicate a potential SARS-CoV-2 infection. Ava COVID-RED is a non-invasive device made up of the following components as illustrated in Figure 3 below:

- *The Ava Bracelet incorporating hardware with electronics and embedded software (Hardware Bracelet Generation 2.0)*
- *A mobile application running on smartphones (iOS and Android)*
- *Backend software, including the COVID-19 infection monitoring algorithm, running on remote servers.*

The wrist-worn bracelet acts as a data logger, recording and storing user's physiological sensor signals as raw datasets throughout the night. The user synchronizes the Ava bracelet to the mobile application (AVA COVID-RED app) the following morning. The mobile app reads out all the raw datasets via Bluetooth Low Energy (BLE) and transfers them to the backend. After computation and pre-processing of the physiological parameters based on the bracelet recordings, the COVID-19 infection monitoring algorithm is run. The obtained pre-processed physiological parameters and potential COVID-19 infection indications are transferred back to the mobile app and displayed to the user.

[figure not shown]

Figure 3: Ava-COVID- Visual of Components

The AVA COVID app is also utilized to collect the Daily Symptom Diary data. The user completes The Daily Symptom Diary in the app, and they will report any symptoms they may be experiencing. The app transfers this information to the backend server and the COVID-19 infection monitoring algorithm is run on the self-reported Daily Symptom Diary data only or in combination with the bracelet data depending on condition. Potential COVID-19 infection indications are transferred back to the mobile app and displayed to the user.

Ava COVID-RED is based on a fertility-related Conformité Européenne (CE) marked predecessor (Ava Fertility Tracker); its codebase was adapted from the Fertility Tracker software, while its hardware component is identical to its predecessor. Along with the hardware, the method of physiological data collection for Ava COVID-RED remains unchanged from its predecessor. The underlying algorithm, however, has been updated to provide a health indicator as opposed to a prediction of the user's fertile window. The Ava Fertility Tracker is still on the market in Europe and North America.

Ava COVID-RED was developed for clinical research purposes only and is not currently on the market in Europe or other countries. The legal manufacturer of the Ava COVID-RED device is Ava AG, [name], Switzerland.

## 6.2 Summary of findings from non-clinical studies

Results of non-clinical studies assessing the device's raw materials and biocompatibility is discussed in Section 6.1 of the most recent version of the Investigational Medical Device Dossier (IMDD). No new biocompatibility testing was conducted for Ava COVID-RED as it used the same underlying hardware as its CE marked predecessor, the Ava Fertility Tracker. Test reports related to the external validation of hardware materials have been appended to the IMDD and include:

- Cytotoxicity Test Report
- Biological Risk Assessment
- Sensitization Test
- Skin Irritation Test Report

Additional non-clinical study data includes findings from a thorough literature evaluation related to the safety profile of wearable devices and COVID-19 detection, documented in Section 6.1.a of the IMDD and the Ava COVID-RED Clinical Evaluation Plan. A summary of the search protocol and its findings can be found in the Ava COVID-RED Clinical Evaluation Plan.

## 6.3 Summary of findings from clinical studies

Results from clinical studies establishing the efficacy of Ava-COVID's predecessor device, including the shared underlying hardware, are described in the Ava COVID-RED Clinical Evaluation Plan. The Clinical Evaluation Plan also outlines the exploratory data analysis which will drive the algorithm development for Ava-COVID. The Clinical Evaluation Plan discusses the clinical evaluation of Ava-COVID, identifying its role in the COVID-RED and COVI-GAPP clinical trials. Findings from these two trials will contribute to the Clinical Evaluation Report, to be written in December 2021 at the end of subject follow-up.

## 6.4 Summary of known and potential risks and benefits

Risk analysis for Ava COVID-RED followed the manufacturer's internal Quality Management System (QMS) specifications. Namely, a Risk management team consisting of representatives from Product, Clinical Development, Quality Affairs, Regulatory, and Software departments. The Risk management team considered both the probability and severity of harm occurring from potential hazards generated by the investigational device. A detailed description of the risk assessment process is outlined in the IMDD, with results from

the investigation provided in the attached Risk Management File (see Risk Management Plan Ava04, Product properties and possible hazards Ava04, FMEA Ava04)

#### **6.5 Description and justification of route of administration and dosage**

Not applicable as this is a wearable device and smartphone app.

#### **6.6 Dosages, dosage modifications and method of administration**

Not applicable as this is a wearable device and smartphone app.

#### **6.7 Preparation and labelling of Investigational Device**

Devices are provided in the commercial package for the Ava Fertility Tracker, consisting of a box with a package insert in English, French, Italian, Spanish, and German languages. A study specific label in the local language will be present on the box before it is handed out to study subjects, and additional study instructions in Dutch will be provided with the package.

#### **6.8 Device accountability**

Devices will be provided by the manufacturer. Prior to handout to the subjects, the devices will be stored centrally as per the manufacturer's instructions. The trial project team is responsible for keeping accurate records of the devices received from the manufacturer as well as the number of devices handed out to and returned by the subjects. Devices will be barcoded and scanned before they are handed out to the subject. At the study's conclusion, the devices must be returned by the study subject to the project team and will be blocked by the manufacturer to prevent off-label use.

**7. NON-INVESTIGATIONAL PRODUCT**

Not applicable.

## 8. METHODS

### 8.1 Study parameters/endpoints

Note that for each parameter and endpoint listed in 8.1.1 and 8.1.2 the measure will be observed in Period 1 and in Period 2. The parameters and endpoints will be statistically assessed within each period separately. See Section 10 for additional details. For the assessment schedule, see APPENDIX 1. Details on the assessments are provided in Section 8.4.

#### 8.1.1 Main study parameter/endpoint

The primary endpoint for this study for each subject is the daily indication of potential SARS-CoV-2 infection as provided by the algorithm based on data from the Daily Symptom Diary (control condition) or the algorithm based on both data from the Daily Symptom Diary and the Ava bracelet (experimental condition). This daily endpoint will be compared against actual SARS-CoV-2 test results (PCR/antigen or serology) collected at baseline, the end of the Learning Phase, and after each Period. For the primary comparison, this daily endpoint will be summarized over each crossover period per subject to determine (1) if a subject was ever judged to have a high risk for a potential SARS-CoV-2 infection, and (2) if a subject was ever confirmed to have a SARS-CoV-2 infection by PCR/antigen or serology testing. For this comparison, parameters such as sensitivity, specificity, positive predictive value, and negative predictive value will be calculated.

#### 8.1.2 Secondary study parameters/endpoints (if applicable)

Additional endpoints will be collected for analysis of the secondary objectives as listed in Section 2.

*Study condition compliance (collected with Ava COVID-RED app)*

- Duration of Ava bracelet use (amount of days between first day of synchronised data and last day of synchronised data)
- Duration of daily symptom diary use (amount of days between first day completed symptom data and last day completed symptom data)
- Compliance rate: percentage of days (as compared to duration of use) that Ava bracelet was worn and synchronised.
- Compliance rate: percentage of days (as compared to duration of use) that symptoms were entered into the Daily Symptom Diary of the Ava COVID-RED app

*Longitudinal characteristics of study population (collected with Ava COVID-RED app)*

- Number/percentage of non-antipyretic and antipyretic medication days
- Number and type of vaccination events
- Number/percentage of days with alcohol consumption
- Number/percentage of days with recreational drug usage
- Number/percentage of days with period (menstruating women only)
- Number of pregnancy events (menstruating women only)

*Overall incidence of SARS-CoV-2 (collected through self-reporting of PCR/antigen test results in the Ava COVID-RED app and serology results)*

- SARS-CoV-2 cumulative incidence by condition and by stratum

*Healthcare Resource Utilization (collected throughout the study through bi-weekly surveys in COVID-RED web portal, structured interviews, and Ava COVID-RED app)*

- Number of COVID-related contacts from subjects to their general practitioner (GP)
- Number and duration of COVID-related hospitalization episodes
- Number and duration of COVID-related intensive care unit (ICU) episodes
- Number and duration of COVID-related supported breathing intervention
- Number and percentage of subjects with each reported medication used during hospitalization (WHO Drug Dictionary [WHO-DD])

*COVID-19 Testing (collected throughout the study through bi-weekly surveys in COVID-RED web portal and Ava COVID-RED app):*

- Number of tests conducted by GGD
- Number of provided PCR kits used
- Number of tests conducted due to red-light indicator of Ava COVID-RED app
- Time between first recommendation for testing and contact with GGD
- Time between first recommendation for testing and contact with study team for PCR sample kit
- Time between first recommendation for testing and GGD SARS-CoV-2 test (stratified for antigen or PCR test if applicable)
- Time between first recommendation for testing and provided PCR SARS-CoV-2 test
- Time between first recommendation for testing and GGD SARS-CoV-2 test result (stratified for antigen or PCR test if applicable)

- Time between first recommendation for testing and Central laboratory SARS-CoV-2 test result

*COVID-19 Vaccination (collected during baseline and throughout the study through bi-weekly surveys in COVID-RED web portal)*

- Number of subjects who received a first and second (where relevant) dose of a COVID-19 vaccination stratified by manufacturer of the vaccine
- Time between first and second (where relevant) dose of the vaccine

*Behaviour (collected throughout the study through bi-weekly surveys in COVID-RED web portal):*

- Number of behavioural changes
- Behavioural changes made and reasons
- Number of behavioural changes (partly) due to the app or wearable
- Behavioural changes (partly) due to the app or wearable and reasons

*Daily Symptom Diary data (collected daily with Ava COVID-RED app)*

- Number and duration of each contiguous reported symptom:
  - Head:
    - Confusion
    - Difficulty concentrating
    - Dizziness
    - Fever
    - Headache
  - Nose and mouth:
    - Bluish lips or face
    - Loss of smell
    - Loss of taste
    - Nasal congestion or runny nose
  - Throat and sternum:
    - Nausea
    - Sore throat
    - Vomiting
  - Chest:
    - Chest tightness, pain or pressure
    - Dry cough

- Shortness of breath or difficulty breathing
- Lower back:
  - Chills or excessive sweating
  - Fatigue
  - Muscle or body aches
  - Skin impurities
- Abdomen:
  - Abdominal pain or cramping
  - Diarrhoea
  - Stomach ache
- General malaise
- No symptoms to report
- Average oral temperature and number/percentage of daily deviations above 38 degrees (Celsius), when collected
- Time between first algorithm indication for testing and symptom onset

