### 2.2 Secondary Objective(s):

1. To assess the health economic utilization of a wearable device and mobile application as measured by endpoints such as:
  - a. Number of tests for suspected SARS-CoV-2 infections
  - b. Number of hospitalizations
  - c. Number of ICU events
  - d. Number of days requiring breathing support (e.g. oxygen and/or ventilation)
2. To determine the incidence of SARS-CoV-2 infection during the study
3. Identify which features of the Ava bracelet and Daily Symptom Diary are the most predictive features
4. Assess the independent predictiveness of an algorithm derived from physiological data gathered by the Ava bracelet in addition to self-reported daily symptom data
5. To assess the time from algorithm indication to symptom onset in the subject
6. To assess the time from algorithm indication to testing of the subject
7. To determine how taking antipyretic medication affects physiological parameters among subjects using the Ava bracelet and Daily Symptom Diary
8. To determine how self-reported vaccinations cause changes in biophysical parameters from subject's given baseline measurements
9. To correlate the longitudinal symptoms reported by study subjects confirmed to have COVID-19 with changes over time in their physiological data
10. To characterise longitudinal symptoms and recovery dynamics reported by the study subjects to the presence or absence of lab-confirmed SARS-CoV-2 infection
11. To assess the adherence to daily symptom diary completion and Ava bracelet wearing and synchronising over time

12. To determine the time necessary to establish baseline physiological parameters per subject in the Learning Phase of the study
13. To determine if retrospective identification of the moment of potential SARS-CoV-2 infection is possible for subjects who are seropositive at the end of a period but were negative at baseline and did not receive an alert to get tested during the study
14. To determine the rate of breakthrough and asymptomatic COVID-19 infections among vaccinated individuals
15. To assess the influence of self-reported COVID-19 vaccinations on compliance to study procedures

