### 3.3 Implementation and development of algorithms

For both the control and experimental conditions, separate algorithms will be applied. For the control condition, an algorithm meant to predict potential active SARS-CoV-2 infections will be applied that incorporates deterministic expert-based rules regarding the presence of SARS-CoV-2 symptoms defined by the Dutch national institute for public health and the environment ‘Rijksinstituut voor Volksgezondheid en Milieu’ (RIVM) guidelines (at the time of writing these include: common cold symptoms [such as a nasal congestion, runny nose, sneezing, sore throat], coughing, shortness of breath, elevated temperature or fever, and sudden loss of smell and/or taste [without nasal congestion]). Any subject that experiences any of the above symptoms will be advised to get tested. For the experimental condition, a machine learning algorithm developed for the same purpose based on both symptom and confounder data as well as physiological parameters collected through the Ava bracelet will be applied on data collected during the study from the Daily Symptom Diary and the Ava bracelet. Both algorithms will give recommendations to the subjects whether they should get tested for SARS-CoV-2 infection. For the algorithm in the experimental condition to give a recommendation based on physiological data, it is first required to establish a baseline per subject of their “normal” physiological patterns. The period of time in which this baseline is determined is referred to as “baselining”. This will take place when subjects enter the study and will not be repeated within each period of the crossover portion of the trial. As soon as a stable baseline has been determined for all measured physiological parameters, the algorithm can start detecting when there are significant deviations from this baseline. For the

remainder of the Learning Phase the experimental condition algorithm will be applied for subjects that are part of this Phase. In Period 1 and 2, data from only the Daily Symptom Diary (control condition) or both the Diary and the bracelet (experimental condition) will be used to inform the algorithms that give indications to the subjects whether they should seek testing.

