### 3.4 Algorithm indicators

In both study conditions, the respective algorithms will alert subjects about their real-time health status in the Ava COVID-RED app through 3 types of indicators:

- **Green light:** No deviations in physical health (symptoms or biophysical parameters) detected. No recommendation is given to the subjects.
- **Yellow light:** Subjects are experiencing some symptoms but not those strictly defined as related to COVID-19 or biophysical parameters deviate slightly from baseline but do not meet the threshold value for a Red light indicator. The Yellow light indicator asks participants to consider self-isolating and keeping an eye on the Ava COVID-RED app the following day.
- **Red light:** Significant changes in biophysical parameters have been detected or symptoms that meet the RIVM criteria have been reported. The Red light indicator suggests subjects consider getting tested for COVID-19 and/or to consult a medical professional.

In all cases of a red-light indicator, subjects will receive the following generic message on the home screen of the Ava COVID-RED app after synchronising their bracelet or logging their symptoms within the last 24 hours:

“Your data suggests changes in physiological parameters and/or symptoms that might be related to a potential COVID-19 infection. Please consider seeking testing and/or input from a medical professional.”

When subjects obtain a positive PCR/antigen or serology test result during the study, they will continue to be in the study but will be moved into a so-called “COVID-positive” mode in the Ava COVID-RED app. This means that they will no longer receive recommendations from the algorithms but can still contribute and track symptom and bracelet data.

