#### 4.4.2 Early detection analysis

The second statistical analysis that will be performed for the primary objective concerns the timing of each study condition to detect SARS-CoV-2. The time to first SARS-CoV-2 indication or infection will thus be compared between the conditions. This will be tested using a stratified log-rank test. Frequently, power calculations for the log-rank test assume some form of proportional hazards or a specific parametric family for the study arms. In this study, we expect the experimental condition to be able to detect SARS-CoV-2 infection earlier due to the possible detection of pre- or asymptomatic individuals due to deviations in physiological parameters. However, when subjects become symptomatic, the algorithms in both the control and experimental condition will each declare subjects to likely be infected at the same moment by definition. To account for this aspect, a piecewise log-rank test power calculation is used to characterize the trial power. The assumption in the piece-wise hazards is that initially the experimental condition will have a higher chance to detect SARS-CoV-2 infection; however, this difference will decrease over time resulting in equal hazards in the later pieces of the hazard function. As described in the first analysis above, the proposed crossover design results in an application of bootstrap statistical testing so that the power calculations in Table 5 are rough approximations. The estimated power is bounded below by a parallel-arm study with 10,000 subjects per condition and above by a study with 20,000 subjects per condition. From these bounds it appears that the trial is well powered under all of the recently reported RIVM data.

Table 5: Lower (10,000) and upper (20,000 ) bounds of the trial power for a piecewise log-rank test to detect differences between study conditions on the time to first SARS-CoV-2 indication or infection based on infection rates of Weeks 36 through 40 of 2020

|              | Week 36 |      | Week 37 |      | Week 38 |      | Week 39 |      | Week 40 |      |
|--------------|---------|------|---------|------|---------|------|---------|------|---------|------|
|              | 10k     | 20k  | 10k     | 20k  | 10k     | 20k  | 10k     | 20k  | 10k     | 20k  |
| Power | 0.66    | 0.92 | 0.80    | 0.98 | 0.94    | 0.99 | 0.99    | 1.00 | 1.00    | 1.00 |

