#### **8.4.11 Receive algorithm-based health indicator**

During follow-up, subjects will be informed by the Ava COVID-RED app whether the algorithm has detected symptoms and/or changes in physiological parameters potentially indicative of a COVID-19 infection. Following onboarding instructions provided by the study team, subjects will then be expected to seek testing for SARS-CoV-2. Algorithms will be used to assess the risk of potential SARS-CoV-2 infection. In the control condition, the algorithm is solely reliant on symptom data entered by the subject during the study and background medical information collected at registration. In the experimental condition, the algorithm is additionally reliant on physiological data collected from the Ava bracelet. If subjects are given a red-light indicator (significant changes in biophysical parameters have been detected or symptoms that meet the RIVM criteria have been reported), they will be advised to seek testing for SARS-CoV-2 infection.

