### 10.5 Analysis of Secondary Endpoint(s)

Secondary study endpoints mentioned in section 8.1.2 will be analysed and compared within the Intention-to-treat, Efficacy analysis and Partial compliance sets within each period. Where deemed relevant, analyses will also be executed within selected subsets of these analysis sets. Specific subsets will be listed within the Statistical Analysis Plan. Results will be presented in tables where possible. Where percentages are to be calculated, the number of subjects in the condition within the specified analysis (sub)set will be used as the denominator.

Where assumptions are met, Cochran-Mantel-Haenszel tests stratified by the risk strata will be performed in each period for multiple secondary endpoints, including:

- The number and percentage of subjects that obtained a red-light indicator by the applied algorithm at least once.
- The number and percentage of subjects with at least one positive SARS-CoV-2 virus test result during follow-up.

- The number and percentage of subjects that donated a blood sample for a SARS-CoV-2 antibody test at baseline, after the Learning Phase and after both periods.
- The number and percentage of subjects with a positive SARS-CoV-2 antibody test at baseline, after the Learning Phase and after both periods.
- The number and percentage of subjects with at least one positive SARS-CoV-2 virus test result during each period OR a positive SARS-CoV-2 antibody test result within those periods.
- The number and percentage of subjects without a positive SARS-CoV-2 virus test result during each period AND a negative SARS-CoV-2 antibody test result within those periods.
- The number and percentage of subjects that have reported experiencing each of the symptoms listed in the Ava COVID-RED app at least for one day during the study.
- The number and percentage of subjects that have reported experiencing each of the symptoms corresponding by the RIVM guidelines at least for one day during the study.
- The number of subjects who reported a positive SARS-CoV-2 virus test during the study and the percentage of subjects who reported a positive SARS-CoV-2 virus test during the study, with the number of subjects ever receiving a PCR test during the study as the denominator.

Where assumptions are met, t-tests will be performed in each period for multiple secondary endpoints, including:

- The average and median number of times a single subject obtained a red-light indicator by the applied algorithm.

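### Comparing lead time from first red light to symptom onset between conditions favours the bracelet whether or not it detects infection, because any false bracelet alarm before onset counts as lead

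*Protocol*

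**What the plan says.** - **Objective.** Protocol section 2.2, objective 5: "To assess the time from algorithm indication to symptom onset in the subject".
- **Endpoint.** The last item of the diary list in section 8.1.2 is "Time between first algorithm indication for testing and symptom onset". The item defines neither onset nor a population, and it sets no limit on how far before onset an indication may fall.
- **Comparison.** Section 10.5: "Secondary study endpoints mentioned in section 8.1.2 will be analysed and compared within the Intention-to-treat, Efficacy analysis and Partial compliance sets", within each period. The endpoint appears in neither the Cochran-Mantel-Haenszel list nor the t-test list. Both lists are open-ended.
- **Control rule.** Section 3.3 says the control algorithm "incorporates deterministic expert-based rules regarding the presence of SARS-CoV-2 symptoms". Section 8.4.11 says that in control "the algorithm is solely reliant on symptom data entered by the subject during the study and background medical information collected at registration".
- **Red light.** Section 3.4 gives the trigger as: "Significant changes in biophysical parameters have been detected or symptoms that meet the RIVM criteria have been reported".
- **Once symptoms appear.** Section 4.4.2 says "the algorithms in both the control and experimental condition will each declare subjects to likely be infected at the same moment by definition".

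**The concern.** Lead time is meant to show how early an algorithm warns before symptoms. In control, the warning is produced by the symptoms themselves, so the endpoint there mostly measures logging delay. In the experimental condition, the warning is the earlier of that same trigger and any bracelet alarm. An alarm that has nothing to do with infection still counts as lead if it falls before a later symptom onset, and more false alarms mean longer apparent lead.

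The contrast therefore cannot separate early detection from false alarms. The hypothesis in section 1.4 is that the combined algorithm detects symptomatic infection earlier, so a positive difference here could be taken as evidence for it. Section 10 applies a two-sided 0.05 level without multiplicity adjustment.

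**Working it through.** The protocol gives no sample size, effect or power for this endpoint, so there is no figure to reproduce. The check has a structural part and an illustrative part.

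**Structure.** Let O be symptom onset, D ≥ 0 the logging delay and B the first bracelet alarm in the period.

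- Control red light: C = O + D (sections 3.3, 3.4, 8.4.11). Section 8.4.9 allows symptoms to be entered up to 7 days late. I assume the light fires when the entry is made.
- Experimental red light: E = min(C, B) (sections 3.4 and 4.4.2).
- Lead in control: O − C = −D ≤ 0, if O is the onset of the symptoms that trigger the light.
- Lead in experimental: O − min(C, B) ≥ O − C.

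For the same subject, the experimental rule can never give a shorter lead than the control rule. Randomisation carries this ordering over to the expected values in the two conditions.

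**Illustration with an uninformative bracelet.** Inputs:

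- A 90-day period, from the 3 months in section 3.1.
- Onset uniform over days 1 to 90 (assumption).
- A bracelet alarm with nightly probability q, independent of illness (assumption; the protocol gives no rate).
- Same-day logging, D = 0.

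Formulas:

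- Share with positive lead: p = 1 − [1 − (1 − q)^90] / (90q)
- Mean lead: 44.5 − p(1 − q)/q, where 44.5 is the mean of O − 1

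For q = 0.002: p = 1 − 0.1649/0.18 = 0.084, and mean lead = 44.5 − 499 × 0.0840 = 2.6 days.

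| q per night | any alarm in 90 days, 1 − (1 − q)^90 | share with lead > 0 | mean lead, experimental | mean lead, control |
|---|---|---|---|---|
| 0.2% | 16.5% | 8.4% | 2.6 d | 0 |
| 0.5% | 36.3% | 19.3% | 6.1 d | 0 |
| 1% | 59.5% | 33.9% | 11.0 d | 0 |
| 2% | 83.8% | 53.5% | 18.3 d | 0 |
| 5% | 99.0% | 78.0% | 29.7 d | 0 |

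A simulation of 200,000 subjects agrees with these means to within 0.03 days. With D uniform on 0 to 7 days, the control mean is −3.5 days. The experimental mean is then −0.6 days at q = 0.2%, 3.3 at 0.5% and 8.7 at 1%.

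**Chance of a significant result.** This uses a Welch t-test at two-sided 0.05, 400 runs and D uniform on 0 to 7. The test is my choice, since the protocol names none. The table shows the share of runs significantly favouring the uninformative bracelet.

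| symptomatic subjects per condition | q = 0.2% | q = 0.5% | q = 1% |
|---|---|---|---|
| 50 | 33% | 93% | 100% |
| 100 | 81% | 100% | 100% |

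**Other reading of onset.** Suppose O is the onset of the confirmed infection, while the indication remains the first red light of the period. An earlier unrelated cold then gives a control subject positive lead. At assumed daily cold rates of 0.2%, 0.5% and 1%, the same formula for p gives 8%, 19% and 34% of control subjects. Adding uninformative alarms lengthens the lead further. With colds and alarms both at 0.2%, the combined daily rate is 1 − 0.998² = 0.003996. The mean then rises from 2.6 days in control to about 4.95 days in experimental (44.5 − 0.15867 × 0.996004/0.003996).

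**The case against.** Five points can be made against the concern.

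1. **The comparison is inferred.** It rests on the general sentence in section 10.5. No test or effect measure is attached to this endpoint, and objective 5 speaks of assessing, not comparing. This stands as a limit on how firmly the protocol commits to a test. The sentence still covers every 8.1.2 item, and the contrast within a period is experimental against control.
2. **Onset and population are matters for the analysis plan.** A reader might infer that the protocol has decided to analyse all subjects, confirmed infection or not. It has not; the item is silent, and section 10.5 leaves subsets to the SAP. What remains is the stated pairing of first indication with onset, compared between these two rules. It favours the bracelet under either definition of onset examined.
3. **Zero is not an absolute ceiling.** A reader might infer that no control subject can ever have positive lead. The documents do not support that, because onset is undefined. Sections 1.4 and 10 also describe the control algorithm as machine-learned or trained, which sits uneasily with the fixed rule in section 3.3. Either way it uses no bracelet data.
4. **The comparator is deliberate.** Section 3.2 defends a symptom-only control as measuring incremental gain. That is accepted. The fault lies in this contrast, not in the control.
5. **Other results would expose a useless bracelet.** Section 10.2 reports specificity and PPV, and section 10.5 compares red-light frequency. Suppose 40% of uninfected subjects log a qualifying symptom and alarms are independent. Specificity then falls from 60% to 60% × (1 − 0.165) = 50% at q = 0.2%, and to 60% × (1 − 0.363) = 38% at q = 0.5%. Table 4 shows power of 1 for a 3-point difference. This stands and lowers the severity, but it does not make the lead-time contrast interpretable.

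**Conclusion.** The point holds as a directional bias in one secondary endpoint. On the protocol's stated triggers, the between-condition lead-time contrast favours the bracelet, and false alarms before onset add to the apparent benefit. The direction rests on the two algorithms firing together once symptoms appear, as section 4.4.2 states.

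The size is not known. The figures of roughly 2.6 to 11 days for nightly alarm rates of 0.2% to 1% depend on assumed alarm rates, uniform onset and no limit on how far back an alarm counts.

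A reader might conclude that the trial would mistake a useless device for a useful one. The documents do not support that, because specificity and PPV are primary measures and early detection has its own analysis in section 10.3. Severity is minor to moderate.

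**What to change.** - State in section 10.5 that this endpoint is excluded from between-condition testing.
- Describe it in subjects with laboratory-confirmed symptomatic infection, with onset defined as onset of that infection.
- Count only indications within a prespecified look-back window before onset. Report the share with any lead and the median lead.
- Benchmark both against the red-light rate in illness-free windows of equal length, and show them beside specificity. A window alone is not enough. If it were 14 days, for illustration, the chance of at least one uninformative alarm, 1 − (1 − q)^14, would be 2.8%, 6.8% and 13.1% at q = 0.2%, 0.5% and 1%.

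The cost is a change of wording in sections 8.1.2 and 10.5 and matching text in the SAP. The data are already collected. The downside is fewer subjects and a less favourable-looking figure.
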